#### 6.6 Data Collection Techniques and Tools:

To assess feasibility, sources of data include study visit attendance, counseling session attendance, and peer support engagement logs. To assess acceptability, a brief exit interview and behavioral survey will be conducted. To assess fidelity, a counseling session checklist will be collected. Additionally, to assess preliminary effectiveness, we will measure BDI-II and viral load at enrollment, 6-month visit, and 12-month visit. PHQ-9 will also be measured at enrollment, 6-month visit, 12-month visit, and each counseling session. For viral load testing, trained counselors will collect drops of participant blood from a finger stick prick and put the drops on a blood collection card. The blood spot collection card will be sent to a laboratory to assess viral load and then it will be stored in a freezer at UNC Project Malawi until the end of the study. The collection card will not have the participant's name or other identifying information attached, only their study ID number. Blood collection cards will be destroyed at the end of the study.

Record Availability: The site investigator will make all data abstraction documents and records readily available for inspection by the local IRB as requested.

For the brief exit interview, a semi-structured interview guide will be developed to explore acceptability of the FB and peer support sessions. All interviews will be digitally recorded, transcribed in Chichewa, and then translated into English by study staff according to a transcription protocol. All transcripts will then be reviewed by the interviewer for transcription and translation accuracy.

#### 6.7 Data Analysis:

Outcomes: The primary goal of this R34 application is to evaluate the feasibility, acceptability, and fidelity of a counseling intervention to improve depression and engagement in HIV care among ALWH. Recognizing the small sample size, indicators of preliminary effectiveness of the intervention for mental health and engagement in care outcomes will be reported as secondary outcomes. Primary and secondary outcomes will be assessed at 6 months and 12 months and compared across the 3 study arms.

##### Primary Outcomes:

- Feasibility: will be defined as the ability to successfully enroll and retain depressed ALWH in the study. Feasibility will be assessed as the number of ALWH enrolled, a comparison of planned to actual enrollment and reasons for non-enrollment, and the proportion of ALWH retained in each arm by the end of the study period. We will also assess the number of sessions that participants attended and peer support engagement during the study period.
- Fidelity: will be defined as adherence to the intervention protocol. Fidelity to content for sessions will be assessed by a member of the research team using a checklist of intervention characteristics. Covering at least 80% of checklist items during each session will be considered fidelity to the intervention protocol.
- Acceptability: will be defined as the ability to deliver and participate in a useful intervention that is appropriate regarding resources and culture. Acceptability will be assessed through brief exit interviews with a sample of ALWH, all study staff, and supervisors. Exit interviews will assess how easy the intervention was to participate in or deliver, the perceived usefulness of the intervention, suggestions for improvement, and will explore contextual factors that impeded or facilitated implementation.

##### Secondary Outcomes:

- Effectiveness will be assessed through changes in three outcomes: 1) depression symptoms ( $\geq 50\%$  change in BDI-II scores from enrollment to the end of the study period), 2) retention in care (whether an ALWH attended at least one appointment per quarter), 3) and viral suppression at 12 months (HIV RNA < 1000 copies/mL).

To assess balance across all 3 study arms at enrollment, we will compare participant characteristics using t-tests for continuous variables and chi-square tests for categorical variables. Quantitative Data: Quantitative measures of feasibility, fidelity, acceptability, and preliminary effectiveness will be summarized using means and standard deviations or proportions and compared across arms using statistical models for continuous or binary outcomes, as appropriate. For feasibility, we will examine the mean number of ALWH enrolled and the proportion of ALWH retained in each of the three study arms (adapted, enhanced, and standard of care). For fidelity, we will examine and compare the proportion of counselors covering at least 80% of checklist items during random direct monitoring sessions across study arms. For acceptability, we will examine and compare the proportion of participants and study staff who found the intervention helpful and easy to deliver across study arms. Changes in depression and engagement in care will be assessed for the 6-month study visit and the 12-month study visit. Generalized estimating equations with an appropriate link for each outcome (i.e., identity link for continuous variables and log link for binary variables) and an exchangeable correlation matrix will be used to examine differences in BDI-II scores, engagement in care, and viral suppression and will account for baseline values of all outcomes and clinic differences. All statistical models will control for any unbalanced confounders. Every effort will be made to minimize missing data, including collecting detailed locator information for the participant as well as for up to two individuals who could help reach the participant should they drop out of contact. However, some missing data is likely to occur. We will examine the data for patterns of missingness and if identified, will conduct sensitivity analyses using inverse probability weights to correct for the bias introduced by the missing data. Qualitative data: Analysis of qualitative exit interview data will involve four steps: 1) reading for content; 2) deductive and inductive coding; 3) data display to identify emerging themes; and 4) interpretation. Codes will be refined during the analysis process and memos will be written for each identified theme.

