#### 6.5 Sample Size Determination

The sample of 105 ALWH (35 per arm) will be sufficient to estimate quantitative measures of feasibility and acceptability with reasonable precision (e.g., confidence intervals around proportions of  $\pm 7$ -9 percentage points across all arms, and  $\pm 9$ -17 percentage points within a given arm).

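### Beyond baseline outcome values and clinic, covariates depend on a balance screen that 35 per arm cannot support, and the weighted sensitivity analysis is run only if a missingness pattern is found

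*Protocol*

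**What the plan says.** All the relevant rules stand in protocol section 6.7, in the paragraph after the secondary outcomes.

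- **Balance.** "To assess balance across all 3 study arms at enrollment", the plan states, "we will compare participant characteristics using t-tests for continuous variables and chi-square tests for categorical variables". No significance level or other threshold is given.
- **Adjustment fixed in advance.** The GEE models "will account for baseline values of all outcomes and clinic differences". No test comes first.
- **Adjustment that depends on the data.** "All statistical models will control for any unbalanced confounders". These confounders are not named.
- **Missing data.** "However, some missing data is likely to occur". The response is: "We will examine the data for patterns of missingness and if identified, will conduct sensitivity analyses using inverse probability weights". The weighted analysis is thus a sensitivity analysis, and the main GEE is unweighted in either case.

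Section 6.5 gives the arm size: "The sample of 105 ALWH (35 per arm) will be sufficient to estimate quantitative measures of feasibility and acceptability with reasonable precision".

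**The concern.** A t-test compares two groups, so with three arms it must be either a set of pairwise tests or loose wording for an analysis of variance. More importantly, a significance test at this size is a poor way to choose covariates. Whether a variable needs adjustment depends on how strongly it predicts the outcome and how far the arms differ, not on whether that difference reaches significance. A screen at 35 per arm passes over most moderate imbalances and sometimes flags variables that do not matter.

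The protocol itself points to likely prognostic variables. Section 6.3 admits ART initiators, re-initiators and established patients and seeks diversity in age, gender identity and acquisition type. Section 2.1 says that the experience of these adolescents differs by how HIV was acquired. None of these is fixed as a covariate.

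The weighted analysis has the same conditional form. Section 2.1 reports higher loss to follow-up in this population. Section 6.1 adds peer support in the Enhanced Friendship Bench arm to help engagement in care, and section 6.6 obtains viral load by finger prick at a study visit. Missingness that differs by arm is therefore foreseeable. A check that is easy to plan should not wait for a pattern to be noticed.

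**Working it through.** **The plan's own figure.** The protocol gives no power for the balance tests. Its only sample-size figure is the precision of a proportion, 1.96 × √(p(1−p)/n). For n = 35 this is ±16.6 points at p = 0.50 and ±9.0 at p = 0.92, which matches the stated 9 to 17. For n = 105 it is ±8.8 at p = 0.70 and ±7.7 at p = 0.80, within the stated 7 to 9. Nothing below depends on it.

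**Inputs.** From the protocol: 35 per arm, three arms. Assumed because not stated: a two-sided 5% level, imbalances of 0.2 to 0.5 SD, covariate-outcome correlations of 0.3 and 0.5.

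**1. What the screen detects.** The standard error of a standardised difference is √(2/35) = 0.239. The critical t on 68 degrees of freedom is about 1.995, so an observed difference must reach 1.995 × 0.239 = 0.48 SD to be flagged. Power from the noncentral t, with noncentrality d/0.239, and from a three-arm F test with the third arm midway:

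| True imbalance | Pairwise t-test | Three-arm F test |
|---|---|---|
| 0.2 SD | 13% | 10% |
| 0.3 SD | 24% | 18% |
| 0.5 SD | 54% | 44% |

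For a binary characteristic compared between two arms, 50% against 60% is flagged 13% of the time, and 50% against 70% is flagged 40% of the time.

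**2. What test-then-adjust does to the estimate.** Simulation with 20,000 runs per setting, 35 against 35, a linear model, outcome SD 1 and no treatment effect. Without adjustment the bias is correlation × imbalance, for example 0.5 × 0.3 = 0.15 SD.

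| Correlation | True imbalance | Bias, test then adjust | Bias, always adjust | SD of estimate, test then adjust | SD of estimate, always adjust |
|---|---|---|---|---|---|
| 0.5 | 0 | 0.00 | 0.00 | 0.231 | 0.209 |
| 0.5 | 0.3 | 0.08 | 0.00 | 0.226 | 0.210 |
| 0.5 | 0.5 | 0.07 | 0.00 | 0.233 | 0.216 |
| 0.3 | 0 | 0.00 | 0.00 | 0.237 | 0.230 |
| 0.3 | 0.3 | 0.05 | 0.00 | 0.238 | 0.234 |
| 0.3 | 0.5 | 0.04 | 0.00 | 0.242 | 0.238 |

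At correlation 0.5, type I error is 5.3% against 4.8% for an imbalance of 0.3 SD, and 6.2% against 5.0% for 0.5 SD. With no true imbalance, the price of testing first is precision: (0.231/0.209)² = 1.22, a variance 22% larger.

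**3. Would the missingness trigger fire?** The protocol does not say how patterns are looked for. If it were a 5% test between two arms of 35, then 10% against 20% missing would be detected 21% of the time, and 10% against 25% would be detected 38% of the time.

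**The case against.** Much can be said for the plan. Baseline values of the outcomes are usually the strongest prognostic covariates, and they are already fixed. Effectiveness is secondary, section 4.0 states no hypotheses, and covariate lists are often left to a statistical analysis plan, which is not shown here. The simulated harm to type I error is small. All of this stands and limits the weight of the point. It does not remove it, because selecting covariates by imbalance and weighting only on a detected pattern are rules written in the protocol, which an analysis plan would have to follow or depart from.

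Several stronger readings are tempting, and the documents do not support them.

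- *All adjustment hangs on the tests.* It does not: baseline outcomes and clinic enter untested. That the tests define imbalance at all is the natural reading, but the protocol does not write it out.
- *The missing-data trigger sets the main result.* It decides only whether a sensitivity analysis is run. The look at patterns is not said to be a significance test, so low power there is conditional on that assumption.
- *An unweighted GEE is valid only if data are missing completely at random.* Missingness that depends only on covariates in a correctly specified mean model does not bias it, so dependence on arm is not by itself enough.
- *Weighting would recover a hidden effect.* Assume that 75% of the standard-of-care arm and 90% of the enhanced arm are tested, with 60% suppressed if tested and 30% if lost. The true rates are 0.75 × 0.60 + 0.25 × 0.30 = 52.5% and 0.90 × 0.60 + 0.10 × 0.30 = 57.0%, while the observed difference is 0. But loss here follows the unseen outcome, which weighting on measured variables need not repair. Counting missing as not suppressed gives 45% and 54%, which is 9 points against a true 4.5.
- *Thirty pairwise tests on ten characteristics give 1.5 false flags.* That requires all ten to be continuous. With five continuous and five categorical there are 5 × 3 + 5 = 20 tests and 1.0 expected flag, and a false flag only adds a covariate.

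**Conclusion.** The concern holds for covariates other than baseline outcome values and clinic, and for the condition placed on the weighted sensitivity analysis. At 35 per arm the screen misses about three quarters of 0.3 SD imbalances and nearly half of 0.5 SD imbalances, assuming a two-sided 5% level. Over the settings simulated, testing first leaves 0.04 to 0.08 SD of bias where a true imbalance exists. With individual randomization no systematic imbalance is expected, and the average cost is mainly precision. The bias figures bear more on allocation by clinic. The protocol is unclear on which applies: the abstract calls the trial individual-level, section 6.4 randomizes clinics, and section 6.1 says both. Because baseline outcomes are already adjusted for, the remaining correlation of other covariates may be nearer 0.3 than 0.5, which puts the effect at the lower end.

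The weight is minor to moderate: secondary outcomes in a pilot without hypotheses, though section 2.2 says that its information will support an application for a larger trial. This is a cheap improvement, best made before outcome data are seen.

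**What to change.** 1. Describe baseline characteristics by arm, with standardised differences if wanted, and drop the significance tests.
2. Replace the rule on unbalanced confounders with a short list named now, for example age, sex, HIV acquisition type and ART status (initiator, re-initiator, established), in addition to the baseline outcome values already fixed.
3. Settle whether clinics or individuals are randomized before keeping clinic adjustment. With four clinics over three arms, at least two arms would have a single clinic, and a clinic effect could not be separated from the arm effect.
4. Run the inverse-probability-weighted sensitivity analysis whatever patterns are seen. Making it the main analysis is a matter of preference and is not needed.
5. For 12-month viral suppression, counting missing as not suppressed may be added, but only as a bounding analysis, because it can overstate the difference.

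The cost is wording, a little programming and a few degrees of freedom. With age linear, sex and acquisition type in two levels each and ART status in three, the list adds 1 + 1 + 1 + 2 = 5 parameters. At n = 105 with a log link for binary outcomes, that is a reason to keep the list short.

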## 6.0 METHODOLOGY

6.1 Design of Study: We will conduct a three-arm individual-level clinical pilot trial across four clinics. Clinics will be randomized either to adapted Friendship Bench (N = 35 ALWH), enhanced friendship bench (N = 35 ALWH), or standard of care (N = 35 ALWH). Participants will all be recruited and followed for 12 months.

The Adapted Friendship Bench (AFB) will be adapted from the existing Friendship Bench intervention protocol to be youth-friendly and address the unique needs of ALWH. Youth friendly adaptation will include selection of young counselors (mixed genders, aged 20-35) who are motivated to work with young people. Counselors will be trained to deliver non-judgmental counseling that respects the privacy and autonomy of ALWH and enables them to make free and informed choices that are relevant to their individual needs. Training will also include discussion of adolescent development and the unique experiences of ALWH related to stigma, disclosure, social relationship issues, and health care access. Counseling sessions will take place in a youth oriented but discrete location within the HIV clinic and be available on weekends to ensure accessibility. AFB will include 6 individual counseling sessions facilitated by counselors attached to one of the study HIV clinics. The first session includes three components called Opening the Mind, Uplifting, and Strengthening, with subsequent sessions building on the first. Opening the Mind refers to the therapeutic process by which, through asking questions, clients are encouraged to open their minds to identify their problems, choose one to work on, identify a feasible solution, and agree on an action plan through an iterative process guided by the counselor. Each structured session lasts 30-45 minutes and will be conducted in a private clinic room in the participant's local language (Chichewa). No specific retention support will be provided, but participants may identify barriers to engagement in HIV care to address during their counseling session. After 4 sessions of individual therapy, the counselor can refer participants not improving or with suicidal ideation to a supervisor trained in mental health to reassess and manage the case. Case management may include additional counseling or pharmacotherapy, at the discretion of the managing clinician.

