Feasibility of ALWH Recruitment: The proposed study will be conducted at 4 comparable, public health centers in Lilongwe District, Malawi: Area 18, Area 25, Kawale, and Lighthouse. Each of the 4 health centers provides ART services, is located in the urban or peri-urban areas of Lilongwe on a main road, and has a monthly ART clinic volume > 115 individuals (age 10-19) who are either initiating care or established patients. We expect 90% will be between the ages of 13-19. Based on studies among ALWH in Malawi, we conservatively estimate 18% will have depression. Assuming an 80% participation rate, enrolling ~6 ALWH presenting with depression (age 13-19) per site per month (35 ALWH total per site) is feasible in 3 months for a total of 105 ALWH in the entire study. Though current government led data collection efforts for ART care in Malawi include adolescents aged 10-19 and our proposed study includes adolescents in a smaller age window (age 13-19), we believe that our conservative recruitment efforts account this mismatch.

Psychosocial Counselor Recruitment: We will recruit 3 young individuals to be psychosocial counselors at each clinic who will provide the 6 individual counseling sessions to participants (approximately 70 sessions per counselor over 4-6 months). Peer Supporter Recruitment: We will recruit 3 peer supporters for the Enhanced FB arm from the Community Advisory Board, Baylor Teen Club Graduates, and YFHS Clinic Experts. We will aim to select peer supporters who are varied in age, gender, and HIV acquisition status. Supervision for the peer supporters will be provided by the study coordinator.

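### Fidelity is defined per session but analysed as a proportion of counselors, which leaves about 3 units per active arm and no scoring of the Enhanced arm's peer sessions

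*Protocol*

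**What the plan says.** - **Definition** (Protocol 6.7, Primary Outcomes): fidelity is adherence to the intervention protocol, rated by a research team member with a checklist. "Covering at least 80% of checklist items during each session will be considered fidelity to the intervention protocol". The unit is the session.
- **Analysis** (Protocol 6.7, paragraph after Secondary Outcomes): the quantity to be examined and compared is "the proportion of counselors covering at least 80% of checklist items during random direct monitoring sessions across study arms". The unit is the counselor.
- **Staffing** (Protocol 6.3): "We will recruit 3 young individuals to be psychosocial counselors at each clinic", with a workload of "approximately 70 sessions per counselor over 4-6 months".
- **Data source** (Protocol 6.6): "To assess fidelity, a counseling session checklist will be collected". Peer support enters section 6.6 through engagement logs, listed under feasibility.
- **Scope:** objective 3.2 concerns the fidelity of the Adapted (AFB) and Enhanced (EFB) protocols. The opening of section 6.7 nevertheless has all primary outcomes compared across the three arms.
- **Precision** (Protocol 6.5): "The sample of 105 ALWH (35 per arm) will be sufficient to estimate quantitative measures of feasibility and acceptability with reasonable precision". Fidelity is not named there.

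**The concern.** The two parts of section 6.7 use different units, and nothing links them. A counselor observed in several sessions may pass some and fail others, and the protocol does not say whether that counselor counts as meeting 80%. Different rules give different answers from the same checklists.

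Counting counselors also reduces a primary outcome to a handful of units, although many sessions are available to sample. Fidelity is part of the first specific objective, and section 2.2 says that the pilot's information will lead to a cluster-randomized trial. A figure that can take only four values tells the designers of that trial little.

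The peer-group sessions are what EFB adds to AFB. If only individual counseling is scored, an AFB versus EFB fidelity comparison covers only the component the two arms share.

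**Working it through.** **1. Counselors per active arm.** Inputs are 35 participants per arm (6.1, 6.5), 6 individual sessions each (6.1) and 3 counselors per clinic (6.3).

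- Sessions per active arm: 35 × 6 = 210.
- Sessions per counselor with 3 counselors: 210 / 3 = 70. This reproduces the protocol's figure exactly, so its own workload implies 3 counselors per active arm.
- Four clinics serve three arms, so an active arm could hold two clinics and 6 counselors. The load would then be 210 / 6 = 35, which does not match.

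**2. What 3 counselors can show.** The possible results are 0/3, 1/3, 2/3 and 3/3. Exact (Clopper-Pearson) 95% intervals:

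| Counselors meeting 80% | 95% interval |
|---|---|
| 2 of 3 | 9-99% |
| 3 of 3 | 29-100% (lower limit 0.025^(1/3) = 0.292) |
| 6 of 6, two-clinic arm | 54-100% (lower limit 0.025^(1/6) = 0.541) |

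**3. Comparing AFB with EFB** (two-sided Fisher exact test).

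- 3 versus 3: the most extreme table, 3/3 against 0/3, gives p = 2 / C(6,3) = 2/20 = 0.10. No result can reach 0.05.
- 6 versus 3: 6/6 against 0/3 gives 1 / C(9,3) = 1/84 = 0.012, and 5/6 against 0/3 gives 6 / C(9,5) = 6/126 = 0.048. But 6/6 against 1/3 gives 3 / C(9,2) = 3/36 = 0.083. Only a near-complete reversal between the arms would register.

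**4. Effect of the missing combining rule.** Assume a true session pass rate of 90% and independent sessions, with 5 sessions monitored per counselor. A counselor passes all five with probability 0.9^5 = 0.59, and passes at least one with probability 1 − 0.1^5, about 1.00. These are two possible rules; the protocol states neither.

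**5. Session as the unit.** The protocol gives no monitored fraction and no intraclass correlation (ICC). Assume 20% of sessions: 0.20 × 210 = 42 per arm, or 14 per counselor. The half-width is z × sqrt(p(1−p) × D / 42), with D = 1 + (14 − 1) × ICC.

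| Fidelity | ICC | D | Half-width, z = 1.96 |
|---|---|---|---|
| 90% | 0 | 1.0 | ±9 points |
| 90% | 0.1 | 2.3 | ±14 points |
| 80% | 0 | 1.0 | ±12 points |
| 80% | 0.1 | 2.3 | ±18 points |
| 80% | 0.2 | 3.6 | ±23 points |

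With 10% monitored (21 per arm), the half-width at 80% is ±17 to ±25 points over the same ICC range. Replacing 1.96 by the t value on 2 degrees of freedom (4.30), to reflect 3 counselors, gives 4.30 × sqrt(0.09 × 2.3 / 42) = ±30 points at 90% and ICC 0.1.

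**The case against.** **The counselors are everyone who delivers the counseling, not a sample, and the trial states no hypotheses.** On this view, reporting that all three met the threshold is a usable pilot description, and an exact interval on three people asks too much. This stands in part: a counselor-level listing is worth keeping. It does not rescue the stated proportion, because section 6.7 also promises a comparison across arms and gives no rule for classing a counselor.

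**The precision statement in section 6.5 is not wrong.** It covers feasibility and acceptability with participants as the unit. This stands; no precision is claimed for fidelity.

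**Session scoring gains less than it seems.** This stands. The ±9 points holds only at 90% fidelity with no clustering, and under a small-sample multiplier much of the gain goes. The firmer reason for the change is that the analysis would then match the definition.

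Three stronger readings are tempting and are not supported:

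- *The fidelity figure must fall as more sessions are monitored.* That needs a rule that every monitored session must pass, which the analysis paragraph does not state.
- *Standard of care will produce a meaningless fidelity result.* Objective 3.2 and the definition tie fidelity to the interventions, and no checklist is described for that arm. The blanket three-arm sentence is mainly a wording fault.
- *Peer sessions are excluded by definition.* The definition speaks generally of sessions and intervention characteristics and could cover them. What can be said is that sections 6.6 and 6.7 do not carry it through: the source is a counseling checklist and the analysis counts counselors, whom section 6.3 recruits separately from the peer supporters.

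**Conclusion.** The point holds. The protocol itself fixes the fidelity analysis, and does so inconsistently, so this is not a detail left for a statistical analysis plan. A per-session definition is analysed per counselor with no combining rule. With 3 counselors in an arm the result has four possible values, 3 of 3 is compatible with 29-100%, and a 3 versus 3 comparison cannot reach p below 0.10. With 6 counselors, 6 of 6 still leaves 54-100%.

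The count of 3 rests on one clinic per active arm. The workload figure supports that, but the protocol is unclear on it: it names four clinics for three arms and describes allocation both by individual and by clinic. If counselors served both active arms, a counselor would not belong to one arm at all, which strengthens the case for the session as unit.

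As written, the EFB peer sessions would go unscored. The size of the precision gain from the fix rests on an assumed monitored fraction and ICC and should not be quoted as a single number.

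**What to change.** 1. In the analysis paragraph of section 6.7, replace the proportion of counselors by the proportion of monitored sessions covering at least 80% of checklist items. Report it descriptively for AFB and EFB separately, list each counselor's result, and give an interval that allows for clustering by counselor and the small number of counselors.
2. State the planned fraction or number of sessions to be monitored per counselor, since precision depends on it.
3. State that fidelity concerns AFB and EFB only, in line with objective 3.2, and exempt it from the three-arm comparison at the start of section 6.7.
4. In sections 6.6 and 6.7, apply the same 80% rule to a sample of the EFB peer-group sessions, reported separately from the individual counseling.

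Items 1 to 3 are wording. Item 4 needs a short additional form and some observation time by existing research staff at the 90-minute peer sessions. That time is not free, because the budget lists two research assistants.
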